### 7.3 Method of Statistical Analysis in Relation to Objectives

Continuous data (data collected on a 5 grade scale will be regarded as continuous) will be analyzed using the non-parametric Wilcoxon Signed Rank Test. For data using a 2-graded scale the McNemar test will be used. Proportions are tested by the McNemar's test if the number of non-equal answers between the assessment time-points is greater than 10 and by the binomial test if less than or equal to 10^46.

P-values below or equal to 5% will be denoted "statistically significant" even though it is recognized that multiple hypotheses are tested. The risk for multiplicity errors will be taken into account when conclusions are drawn.

### 7.4 Determination of Sample Size

This study aims to look at change in NBD score (range from 0 (very minor bowel dysfunction) to 47 (severe bowel dysfunction)) after introducing TAI with the Navina Smart system in a population with a common feature of having neurological bowel dysfunction. Each patient serves as his/her own control, by measuring change in NBD score before and after treatment with the Navina Smart system. The NBD score is a validated questionnaire and tool that correlates neurological bowel dysfunction to QoL. In this study a patient friendly version of the NBD Score will be used.

To determine the sample size of the study the following formula is used, referred to in Lachin 1981, considering the fact that a pair wise comparison is made.

$$N = \frac{(Z_{\alpha} + Z_{\beta})^2 \sigma^2}{\mu_1^2}$$

Where:

$\mu_1$  = minimal important difference or difference worth detecting

N = Total number of patients

$Z_{\alpha} = 1.96$  (5% two-sided significance level)

$Z_{\beta} = 1.28$  ( $1-\beta = 0.90$ ), 90% power or 0.84 ( $1-\beta = 0.80$ ), 80% power

$\sigma$  = standard deviation of difference in NBD score between baseline (without Navina™) and 3 months use of Navina™.

The table below shows number of patients needed using different levels of minimal important difference and standard deviations, using 90% power and 5% two-sided significance level.

Total sample size for paired observations where  $\sigma$  is known and defined as standard deviation of difference between baseline and follow-up.

| $\mu 1$    | $\sigma = 2.0$ | $\sigma = 2.1$ | $\sigma = 2.2$ | $\sigma = 2.5$ |
|------------|----------------|----------------|----------------|----------------|
| 0.8 | 66             | 73             | 80             | 103            |
| 1.0 | 43             | 47             | 51             | 66             |
| 1.2 | 30             | 33             | 36             | 46             |
| 1.5 | 19             | 21             | 23             | 30             |
| 2.0 | 11             | 12             | 13             | 17             |
| 2.5 | 7              | 8              | 9              | 11             |

The chosen minimal important difference for the study is related to the fact that also small difference could be clinically meaningful for the patients. In addition, depending on baseline NBD score level, smaller, but still valid, changes may be present when starting at a level closer to the inclusion cut of 10 than if the starting point is around 14. For this reason we believe a minimal important difference level valuable to detect in the study of ~0.8 would be representative.

Christensen et al describe in their sample published in 2008 a mean difference in NBD score of -4.5 with corresponding 95% confidence interval of -6.6 to -2.4 after introducing TAI for a 10 weeks' period. This indicates that the expected standard deviation for the difference between baseline and follow up in NBD score would lie somewhere around 2.1-2.2. For detection of a minimal important difference of 0.8, with an expected standard deviation of 2.2, a total of 80 (90% power) subjects who has been using Navina Smart for 3 months are required. However, since higher variability than expected and high drop-out rates may risk the final numbers additional patients must be accounted for. For example, Gosselink et al. reported a discontinuation rate of 55% when introducing TAI therapy in their sample reported in 2004 and Christensen et al. observed a discontinuation rate of 45%, why it is recommended to recruit at least 150 patients in the current study. This will allow 70 of 150 (47%) to drop-out from the study with maintained 90% power to detect a difference of 0.8 between a baseline NBD score (without Navina Smart) and after using Navina Smart for 3 months.

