## 7.5 Statistical Analyses During the Course of the Study

Estimates on minimal important difference and standard deviation may be checked as part of an adaptive statistical design and conditional sample size estimation by interim analysis of a selection of patients, e.g. approximately 60 patients. If the variability is found to be higher and/or the minimal important difference is found to be lower the study is at risk of being inconclusive. In such case additional subjects or premature discontinuation may be considered.

Once the target number of evaluable subjects is secured, i.e. 90% power of the primary variable is verified, partial clean file and analysis of the primary variable and baseline demography will be performed. It is acknowledged that analyses of primary variables and baseline demography will be performed before analyses of secondary variables and analyses of the complete data set. All

analyses will follow the Data Management Plan and be performed on locked data, declared for partial clean file or clean file for the complete data set.

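### The planning SD of 2.1-2.2 in section 7.4 matches the half-width of a published 95% CI, not a patient-level SD, so the claimed 90% power for a 0.8-point change has no valid basis

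*Protocol*

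**What the plan says.** Section 7.4 sizes the trial with a one-sample formula for paired differences, "using 90% power and 5% two-sided significance level". The sigma in the sample size table "is known and defined as standard deviation of difference between baseline and follow-up", so it is the spread of individual patients' changes.

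The target is set as a "minimal important difference level valuable to detect in the study of ~0.8 would be representative". The SD comes from one cited irrigation study, which reported "a mean difference in NBD score of -4.5 with corresponding 95% confidence interval of -6.6 to -2.4" after 10 weeks. The protocol continues: "This indicates that the expected standard deviation for the difference between baseline and follow up in NBD score would lie somewhere around 2.1-2.2". It shows no conversion and does not give the size of the cited sample.

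The sample size follows: "with an expected standard deviation of 2.2, a total of 80 (90% power) subjects who has been using Navina Smart for 3 months are required". Recruitment is set at 150, and the protocol concludes: "This will allow 70 of 150 (47%) to drop-out from the study with maintained 90% power to detect a difference of 0.8".

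Section 7.5 adds that "Estimates on minimal important difference and standard deviation may be checked as part of an adaptive statistical design and conditional sample size estimation", for example at about 60 patients. It also makes the primary analysis wait until 90% power for the primary variable has been verified.

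**The concern.** The lower planning value, 2.1, is exactly half the width of the cited interval. A CI for a mean describes how precisely the mean is known and narrows as the sample grows. The SD of individual changes does not. Reading one as the other understates the SD by a factor of about sqrt(n)/1.96, where n is the size of the cited sample.

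This is the only power justification for the primary endpoint, and section 1.1 calls a sufficiently powered study essential. The 80 evaluable subjects, the 47% drop-out allowance and the power statement all inherit the input. So does the condition in section 7.5, because power can only be verified against some stated difference and the only one given is 0.8.

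**Working it through.** **Inputs, all from section 7.4.** Two-sided 5% (Z = 1.96); 90% power (Z = 1.28); target 0.8 points; planning SD 2.2; cited mean change -4.5 with 95% CI -6.6 to -2.4; 150 recruited, of whom 70 may drop out.

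**Step 1: reproduce the protocol's figure.** N = (1.96 + 1.28)² × 2.2² / 0.8² = 79.4, so 80. Power at 80 is 90.2% by the normal approximation. The table reproduces to within one patient, and 150 - 70 = 80. The arithmetic from the SD onwards is correct, so only the SD is in question.

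**Step 2: what the CI gives.** Half-width = (6.6 - 2.4)/2 = 2.1. Standard error = 2.1/1.96 = 1.07. For a one-sample CI of a mean paired change, half-width = t(0.975, n-1) × SD/sqrt(n), so

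SD = 2.1 × sqrt(n) / t(0.975, n-1).

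**Step 3: which n would justify 2.1-2.2?** With 1.96 in place of t, n = (1.96 × SD/2.1)², which is 3.8 for SD 2.1 and 4.2 for SD 2.2. With the t quantile, n = 6 gives SD 2.0 and n = 7 gives 2.27, so n lies between 6 and 7.

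**Step 4: consequence for a range of n.** The cited n is an assumption. The SD is t-based. Power = Phi(0.8 × sqrt(N)/SD - 1.96). Evaluable subjects needed = (1.96 + 1.2816)² × SD²/0.8². Detectable difference at 80 with 90% power = (1.96 + 1.2816) × SD/sqrt(80).

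| Assumed cited n | SD | Power for 0.8, 80 evaluable | Power for 0.8, 150 evaluable | Evaluable needed for 0.8 | Detectable at 80 |
|---|---|---|---|---|---|
| 10 | 2.9 | 68% | 92% | 142 | 1.1 |
| 20 | 4.5 | 36% | 59% | 331 | 1.6 |
| 40 | 6.6 | 19% | 32% | 708 | 2.4 |
| 60 | 8.1 | 14% | 23% | 1,085 | 2.9 |
| 100 | 10.6 | 10% | 15% | 1,839 | 3.8 |

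Worked case, n = 20: SD = 2.1 × 4.472/2.093 = 4.49; power = Phi(0.8 × 8.944/4.49 - 1.96) = Phi(-0.37) = 36%.

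**Step 5: the cited effect.** At the largest SD in the table, power for 4.5 points with 80 evaluable is Phi(4.5 × 8.944/10.58 - 1.96) = Phi(1.84), about 97%. It is higher at every smaller n.

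**The case against.** The protocol does not say that it used the half-width, and 2.2 is not the half-width. The derivation is therefore inferred. That does not rescue the figure: however it was reached, the text says the CI indicates this SD, and it does so only for a cohort of about 4 to 7 patients.

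The protocol also anticipates trouble. Section 7.4 mentions higher variability than expected as a reason to recruit more, and section 7.5 allows a check of the SD with added subjects. Both soften the error without curing it. The 70-subject margin is spent entirely on drop-out in the protocol's own sum, the table stops at an SD of 2.5, and the interim check is optional.

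A reader might infer more than the documents support:

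- That true power is 10-36%. This range needs a cited cohort of 20 to 100. At 10 patients power would be 68% with 80 evaluable and 92% with all 150. The conversion also assumes a simple one-sample CI of the paired change, which cannot be checked here.
- That the trial cannot detect 0.8 points, or that the interim check would almost certainly find an SD two to four times the plan. Low power is not impossibility, and the second statement again depends on the unstated n.
- That the main comparison is endangered or 150 is too few. For an effect like the cited one, 80 evaluable subjects are ample across the range shown.

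**Conclusion.** The point holds in this form: the SD of 2.1-2.2 does not follow from the cited CI, and the two statements of 90% power for 0.8 points at 80 evaluable subjects are unsupported. This can be shown from section 7.4 alone.

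The size of the shortfall is conditional on the cited cohort. From about 10 patients upwards, power at 80 falls clearly below 90%: 68% at 10, down to 10% at 100. The figures rest on a one-sample CI, a t-based SD and normal-approximation power, as in the protocol's own formula. The planned Wilcoxon signed-rank test would not change the conclusion.

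The defect is the 0.8-point power claim, not the ability to detect an effect of the size cited. It needs correcting because it is the stated basis of the sample size and feeds the power condition in section 7.5. From an assumed cohort of 20 upwards, that condition could not be met for 0.8 within 150 subjects, since 331 or more evaluable would be needed.

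**What to change.** In section 7.4:

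- Give the size of the cited cohort and recompute the SD as half-width × sqrt(n) / t(0.975, n-1).
- Extend the sigma columns of the table to cover the result (about 3 to 11 for cohorts of 10 to 100).
- Replace both 0.8 power statements with the mean change that 80 evaluable subjects detect with 90% power, and say plainly that the trial is not powered for 0.8. The figure must come from the cited cohort's n; the table above only brackets it at 1.1 to 3.8 points.
- Keep N = 150.

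In section 7.5, tie both the interim SD check and the condition that 90% power be verified to the restated detectable difference. Otherwise the primary analysis would still wait on a target that the trial may be unable to meet.

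The cost is rewording in two sections and one recalculated table, with no extra patients. The downside is a less favourable stated detectable difference, and the protocol must acknowledge that a change it calls minimally important lies below what the trial is sized to detect.

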### 7.2 Description of Analysis Sets

The study will be analysed using a Per Protocol (PP) and an Intention To Treat (ITT) approach. Subjects fulfilling the inclusion criteria but none of the exclusion criteria and have been treated according to the protocol without any major deviations will be included in the PP analysis set. All correctly included patients will be included in the ITT analysis set. All treated subjects will be included in the safety analysis set. Treatment efficacy related conclusions will be based on the results from the PP analysis and confirmed by an analysis of the ITT analysis set (only for the primary objective) and demography and treatment safety related conclusions will be based on the results from the safety analysis set.

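### The stated tolerance of 70 drop-outs at 90% power counts three-month users, but efficacy is concluded from the per-protocol set with a Wilcoxon test, and nothing is reserved for either

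*Protocol*

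**What the plan says.** Section 7.4 of the protocol uses a paired-difference formula with the SD taken as known, "using 90% power and 5% two-sided significance level". It sets the inputs thus: "For detection of a minimal important difference of 0.8, with an expected standard deviation of 2.2". From these it concludes that "a total of 80 (90% power) subjects who has been using Navina Smart for 3 months are required". It then recommends recruiting at least 150, giving unexpected variability and high drop-out as the reasons for the margin, and states: "This will allow 70 of 150 (47%) to drop-out from the study with maintained 90% power to detect a difference of 0.8".

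Three other sections bear on whom that number counts and how they are analysed:

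- Section 7.2: "Treatment efficacy related conclusions will be based on the results from the PP analysis". The PP set takes eligible subjects treated without major deviations. The ITT set only confirms the result for the primary objective.
- Section 7.3: continuous data "will be analyzed using the non-parametric Wilcoxon Signed Rank Test".
- Section 7.5 starts the partial clean file and the primary analysis as follows: "Once the target number of evaluable subjects is secured, i.e. 90% power of the primary variable is verified".

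Sections 3.1 and 7.1.3 allow recruitment to be prolonged until enough evaluable subjects are available. The protocol does not say whether that term means three-month users or PP subjects. Section 7.1.3 also states that missing data are not imputed.

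**The concern.** The sample size counts one population and the conclusion is drawn from another that can only be the same size or smaller. A subject can use the device for three months and still leave the PP analysis, for example by breaching a section 4.4 restriction (changed laxatives, newly started opioids, prokinetics, anticoagulants or long-term steroids). A subject can also lack the three-month NBD score, which is completed in the app, e-mailed and uploaded by site staff (sections 6.4.1 and 8.1.1). Section 7.4 reserves no subjects for these losses.

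The named test also differs from the one behind the formula, so part of the shortfall arises even with no exclusions.

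Two things are at stake. The power and drop-out tolerance quoted for the study do not describe the analysis that decides efficacy. And section 7.5 starts that analysis on a count whose only numerical anchor in the protocol is 80 three-month users.

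**Working it through.** **Inputs.** Difference 0.8, SD of the paired difference 2.2, Z values 1.96 and 1.28, 80 required, 150 recruited, 70 drop-outs allowed (all section 7.4); PP set as the basis for efficacy (7.2); Wilcoxon signed rank test (7.3). The PP exclusion rate is not in the protocol, so it is varied as an assumption.

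**1. The plan's own figures.** N = (1.96 + 1.28)² × 2.2² / 0.8² = 10.498 × 4.84 / 0.64 = 79.4, rounded up to 80. Then 150 − 70 = 80 and 70/150 = 46.7%. Both figures reproduce. Nothing is left once drop-out has been taken off.

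**2. Power of the test that the formula assumes.** Power = Φ(√n × 0.8/2.2 − 1.96). At n = 80: √80 × 0.3636 = 3.2525; 3.2525 − 1.96 = 1.2925; power 90.2%. At n = 79 it is 89.8%. So under this test 90% holds for the PP analysis only if all 80 remaining users are in the PP set.

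**3. Power of the test that section 7.3 names.** If the differences are normal, the asymptotic efficiency of the signed rank test relative to the test of the mean is 3/π = 0.955. At n = 80 the effective size is 80 × 0.955 = 76.4; √76.4 × 0.3636 − 1.96 = 1.218; power 88.8%. Simulation with normal differences (mean 0.8, SD 2.2) gives about 88% at n = 80 and about 90% at n = 84. The size required is 79.4 / 0.955 = 83.1, so 84. This step needs no exclusion rate.

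**4. PP exclusions among the 80 who remain (assumed rates).**

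| Assumed exclusion | PP n | Power, normal test | Power, Wilcoxon efficiency |
|---|---|---|---|
| 0% | 80 | 90.2% | 88.8% |
| 5% | 76 | 88.7% | 87.2% |
| 10% | 72 | 87.0% | 85.4% |
| 20% | 64 | 82.9% | 81.1% |

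**5. Drop-out that still leaves 80 PP subjects.** Users needed = 80/(1 − rate), rounded up: 85, 89 and 100 at 5%, 10% and 20%. That leaves 65 (43%), 61 (41%) and 50 (33%) drop-outs out of 150, against the stated 70 (47%).

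**6. Combined loss that keeps 90% under the Wilcoxon test.** 150 − 84 = 66, which is 44% of 150, counting drop-out and PP exclusion together.

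**The case against.** The strongest case on the other side has five parts.

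- **The arithmetic is right.** This stands: 80 and 150 follow from the stated inputs. The fault lies in which subjects and which test the 80 is applied to.
- **PP exclusions and drop-outs overlap.** Sections 4.5.1 and 4.5.2 discontinue subjects for severe non-compliance and incorrect enrolment, and a footnote in section 4.3 does so for a baseline NBD score below 10. Some deviators are therefore already among the 70, and treating all deviations as extra loss would double count. This stands, and it is why the rates in step 4 apply only to the 80 who remain.
- **Recruitment can continue.** Sections 3.1 and 7.1.3 allow extension, section 7.4 says at least 150, and section 7.5 refers to verified power. This softens the point without closing it: extension is optional, section 7.1.3 ties it to drop-out above the allowance, and the subjects to be counted are not defined.
- **Definitions belong in the SAP.** Detailed criteria for a major deviation may well be there. But the power claim and the analysis trigger are in the protocol, and they have to refer to the set that section 7.2 names.
- **The Wilcoxon loss is small and depends on normality.** This is fair. It is one to two points, and with heavier-tailed differences the signed rank test can be the more efficient of the two. Normality is nevertheless the working model of the section 7.4 formula.

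A reader might infer that the primary analysis is bound to be badly underpowered, or that the database will be locked with too few PP subjects. The documents support neither. The PP loss depends on an exclusion rate that they do not give, and an early lock follows only if evaluable is read as any three-month user.

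**Conclusion.** The point holds in limited form. As written, the tolerance of 70 drop-outs at 90% power does not describe the deciding analysis. For the PP set it requires that none of the 80 is excluded or lacks the three-month score. Under the named test, with the plan's inputs and normal differences, power at 80 is about 88–89% even then, and about 84 subjects are needed.

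The further loss from PP exclusions is conditional. Under Wilcoxon efficiency, power falls to 87.2–85.4% at an assumed 5–10% and to 81.1% at an assumed 20%. All of this applies to a true difference of 0.8 with SD 2.2. Section 7.4 also quotes a published mean change of −4.5; for an effect of that size with SD 2.2, these losses would not matter.

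The SD of 2.2 is a separate and larger issue and is not judged here. The mismatch between the set counted and the set analysed remains whatever SD is used. It should be corrected, because the figure is relied on for recruitment and for the section 7.5 trigger.

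**What to change.** 1. In sections 7.4 and 7.5, define evaluable subjects as PP subjects with NBD scores at baseline and at three months.
2. Restate the allowance as total loss from drop-out and PP exclusion combined, choosing one of two statements: either up to 70 of 150 may be lost, leaving 80, with about 88–89% power under the Wilcoxon test; or at most 66 of 150 (44%) may be lost, leaving 84, for 90% power. Do not claim 90% together with a loss of 70.
3. State that the power figure assumes normally distributed differences and the plan's SD.
4. Make the section 7.5 trigger, and the recruitment extension in sections 3.1 and 7.1.3, use the same PP count.

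Keep 150. The change is one of wording, and the quoted tolerance or power becomes slightly less favourable. No increase in the planned number follows from the change itself. If the combined loss exceeds the stated limit, the existing option to extend recruitment would apply to the PP count and could then add subjects.

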## 7.5 Statistical Analyses During the Course of the Study

Estimates on minimal important difference and standard deviation may be checked as part of an adaptive statistical design and conditional sample size estimation by interim analysis of a selection of patients, e.g. approximately 60 patients. If the variability is found to be higher and/or the minimal important difference is found to be lower the study is at risk of being inconclusive. In such case additional subjects or premature discontinuation may be considered.

Once the target number of evaluable subjects is secured, i.e. 90% power of the primary variable is verified, partial clean file and analysis of the primary variable and baseline demography will be performed. It is acknowledged that analyses of primary variables and baseline demography will be performed before analyses of secondary variables and analyses of the complete data set. All

analyses will follow the Data Management Plan and be performed on locked data, declared for partial clean file or clean file for the complete data set.

## 8 DATA MANAGEMENT

Data Management activities will be performed by subjects, site personnel and WHC or their representatives. See Appendix E for an overview of the data flow in the study.

### 8.1 Electronic Data Capture

Data Entry into a central database will be made using Electronic Data Capture (EDC).

Data Entry will mainly be performed by the subjects, but will be performed by study site personnel in cases where EDC is not possible for the subject, *i.e.* where questionnaires are completed using pen and paper (e.g. all EQ-5D-3L forms), for Screening and Demographic variables as well as for AEs and Concomitant Medication.

Data will be entered into eCRFs using Viedoc, a web based EDC system used by WHC. Trained and authorized study site personnel will be responsible for entering data into Viedoc. Data entered into Viedoc will be immediately saved to a central database, hosted by a 3rd party, Pharma Consulting Group Solutions AB.

Study site personnel will enrol subjects using Viedoc. Upon enrolment in the study each subject will be automatically allocated a specific Subject ID (Enrolment number). This is the only identifier used on any study data and the key (the Subject Enrolment and Identification Log) connecting a specific subject to his/her Subject ID will be kept by the Investigator in the Investigator's Study File which is stored securely at the study site.

Subjects will use a site-specific tablet computer to self-report ePRO data using ViedocMe. ViedocMe is the patient interface application of the eCRF and subject specific log-in details will be provided to the subject by site personnel. Upon completion of an ePRO the data will be automatically entered into Viedoc and thus stored in the central database.

The EQ-5D forms will be completed in paper by the subjects.

Subjects unable to complete ePRO will use pen and paper instead. If pen and paper are used, trained authorized study site personnel will enter the data into Viedoc.

